## Abstract

**Background:**

Nurse researchers often face challenges in publishing their work due to limited writing skills, inadequate mentorship, and insufficient institutional support. Strengthening research dissemination is essential for improving evidence-based practice, professional growth, and the visibility of nursing scholarship.

**Objective:**

Thisprotocol aims to identify barriers and facilitators to research publication among nurse researchers and to evaluate the effectiveness of a Mentored Writing Retreat Programme (MWRP) in optimizing the publication process.

**Methods:**

A participatory action research design will be adopted and implemented in two phases. **Phase I** will examine publication barriers and facilitators through a survey and focus group discussions among nurse researchers across Karnataka (*n* = 317). **Phase II** will use a quasi-experimental pre-test–post-test design with intervention and control groups (*n* = 50 per group). The MWRP will be developed based on Phase I findings and will include structured workshops, mentoring, and guided manuscript development over four months, followed by structured follow-up after six months post-intervention.

**Expected Outcomes:**

The protocol is expected to generate comprehensive evidence on challenges affecting research publication and to determine whether a structured writing retreat improves writing skills, increases publication readiness, and enhances scholarly productivity among nurse researchers. The findings will help inform future strategies to strengthen research capacity and enhance publication outcomes in nursing.

Protocol Outline:

**Specifications table**

**Table utbl0001:** 

Subject area	Medicine and Dentistry
**More specific subject area**	Scientific writing, research publication, and mentoring interventions for nurse researchers
**Name of your protocol**	Mentored Writing Retreat to Strengthen Research Publication Among Nurses
**Reagents/tools**	**Demographic Proforma** **DiaZePam Survey Questionnaire** Focus group Interview guide **Structured Knowledge Questionnaire** **Attitude Scale** **Publication Efficacy Scale** **Publication Status Checklist**
**Experimental design**	A two-phase participatory action research (PAR) design: **Phase I:** Survey and focus group discussions to identify barriers and facilitators to research publication among nurse researchers. **Phase II:** Quasi-experimental pretest–posttest design evaluating the impact of a Mentored Writing Retreat Programme (MWRP) delivered through three structured workshops over four months.
**Trial registration**	CTRI/2023/09/057470 [Registered on: 12/09/2023]
**Ethics**	This study was approved by the Institutional Ethics Committee of Kasturba Medical College(KMC), Manipal. **Human subjects statement:** Informed consent was obtained from all participants prior to survey participation, focus group discussions, and enrolment in the intervention programme. **Animal research:** Not applicable—this study does not involve animal subjects. **Social media data:** Not applicable—no social media data were used.
**Value of the Protocol**	• Provides a structured, replicable model (MWRP) to enhance writing skills, publication efficacy, and scholarly productivity among nurse researchers. • Uses participatory action research to co-develop a publication manual and tailor training based on real-world barriers and facilitators. • Supports capacity-building and strengthens research dissemination in nursing institutions, contributing to improved evidence-based practice.

## Background

Scientific evidence forms the basis for improving clinical decision-making and patient outcomes, and its dissemination through publication is essential for strengthening nursing practice[1,2]. Nursing research continuously generates new knowledge, while evidence-based practice ensures that this knowledge is appropriately translated into clinical care [3,4]. The ability to communicate research findings effectively through scientific writing is therefore crucial for expanding the evidence base within the nursing profession [5]. For this reason, training programmes that enhance research communication skills and support the translation of evidence into practice are increasingly emphasized in health sciences education[6].

Despite the growing need for scholarly output, nurses and other health professionals face significant challenges in preparing manuscripts and navigating the publication process. Several studies across health sciences have identified barriers such as limited writing skills, inadequate mentorship, lack of institutional support, low research confidence, and limited awareness of journal requirements [[7], [8], [9]]. Rejection of manuscripts due to poor scientific writing remains common, highlighting the importance of targeted writing support for researchers[10]. Structured scientific writing programmes including workshops, peer writing groups, and editorial mentoring have been shown to enhance writing proficiency and support manuscript development[[11], [12], [13]].

The academic context in India underscores an urgent need for initiatives that strengthen scientific writing capacity. Although research output is increasing, concerns persist regarding the quality of publications [14]. An analysis of research productivity in Indian institutions indicated substantial variability, with many colleges producing few or no publications over extended periods[15]. Challenges in manuscript writing, journal selection, and submission procedures have been consistently reported among researchers across disciplines[16]. Interventions such as writing workshops and coaching programmes have been recommended to address these gaps[17,18]. For nursing professionals in particular, structured writing support has been associated with improved writing confidence and manuscript completion[19].

Barriers to publication are multifaceted. External challenges include limited funding, insufficient research infrastructure, high publication charges, and prolonged review times [20,21]. Internal barriers include lack of time, inadequate writing skills, and difficulty with academic English[22,23]. The availability of mentorship, technical guidance, and feedback mechanisms has been identified as a key facilitator for overcoming these obstacles[20,24]. Previous studies also highlight that although many nursing faculty members show positive attitudes toward research, confidence in writing and publishing remains limited [25,26].

These contextual factors indicate the need for structured, practical, and accessible scientific writing support models for academic nurses. Short-term, focused writing programmes may offer an efficient approach for researchers who cannot participate in long-duration research courses[27]. This protocol is situated within this broader context. It outlines a structured approach to exploring publication challenges among nurse researchers and describes the development of a Mentored Writing Retreat Programme designed to address skill-based needs through a participatory, capacity-building process.

## Description of protocol

This protocol provides a reproducible, step-by-step method to optimise research publication among nurse researchers through the Mentored Writing Retreat Programme (MWRP) developed using Participatory Action Research (PAR). The protocol is designed to enable other researchers and academic institutions to replicate the intervention, data collection methods, and evaluation procedures.

### Study design

A participatory action research approach will be used throughout the study. Participatory action research (PAR) refers to a research method, typically concerned with organizational self-assessment, in which the subjects of the study"participate with the professional researcher throughout the research process from the initial design to the final presentation of the results and discussion of their action implications [28]

#### Design framework

Participatory Action Research (PAR) involves four phases,1) plan, 2) act, 3) observe and 4) reflect [29]. A detailed study design framework using PAR in the implementation of MWRP is depicted in Fig. 1.

**Fig. 1 fig0001:**
[figure not shown]
Framework of MWRP.

The development and implementation of the MWRP will follow four iterative PAR cycles:•Plan: Identification of barriers and facilitators through surveys and focus group discussions.•Act: Development and implementation of the MWRP and research publication manual.•Observe: Monitoring participant progress, engagement, and outcomes during workshops and mentoring.•Reflect: Evaluation of feedback from participants and mentors to refine workshop content, mentoring strategies, and delivery methods.

Each cycle will inform subsequent modifications, ensuring that the programme remains contextually relevant, responsive to participant needs, and continuously improved.

*Phase 1: Exploratory Survey on Barriers and Facilitators for Research Publication.*

Phase I of the study is structured as an explorative investigation aiming to identify the barriers and facilitators for research publication as perceived by nursing professionals employed in nursing institutions. This phase employs a combination of methods, including a descriptive survey and focus group discussions.

The primary objective of Phase I is to gain insights into the challenges and supportive factors encountered by nursing professionals in the process of publishing research findings. Through the descriptive survey, participants will provide valuable information regarding their experiences, perceptions, and the various obstacles hindering or facilitating their engagement in research publication activities.

Additionally, focus group discussions will be conducted to delve deeper into the identified themes and gather rich qualitative data. These discussions will offer a platform for participants to express their perspectives, share experiences, and offer suggestions for overcoming barriers to research publication.

The findings from Phase I will serve as a foundation for informing the development and implementation of interventions aimed at enhancing the research publication process among nurse researchers.

*Phase 2: Impact of Mentored Writing Retreat Programme (MWRP).*

In Phase II, the study shifts focus towards evaluating the impact of the Mentored Writing Retreat Programme (MWRP) on optimizing the research publication process among nurse researchers. This phase adopts a quasi-experimental design, specifically employing a Pretest-Posttest approach with both control and interventional groups.

Before the implementation of the MWRP, pre-test assessments will be administered to nurse researchers in both the interventional and control groups. These assessments will cover key domains including knowledge, attitude, publication efficacy, and publication status. This baseline assessment will provide a benchmark against which post-intervention outcomes can be compared.

Subsequently, the Writing Retreat Program will be developed based on the identified needs and requirements of nurse researchers, as revealed through a comprehensive need assessment survey. The intervention will be exclusively implemented for the nurse researchers in the interventional group through a series of three workshops, each spanning eight hours and covering relevant content areas, activities, learning materials, and feedback mechanisms.

Throughout the workshops, participants will be assigned writing tasks after each session, which will then be reviewed by the workshop facilitator. This iterative process aims to provide personalized feedback and guidance to participants, thereby enhancing their writing skills and proficiency. Following the completion of the workshops, post-testing will be conducted to assess changes in knowledge, attitude, publication efficacy, and publication status among both the control and intervention groups at four months following the conclusion of the final workshop session. The publication status will also be assessed after a six-month follow-up.

### Setting

The setting of the study will encompass nursing institutions affiliated with health sciences universities in Karnataka, India, where nursing faculty members holding MSc or PhD qualifications, as well as those currently pursuing PhDs, will be targeted for participation. With over 500 nursing colleges distributed across Karnataka, this setting offers a diverse landscape for exploring research publication experiences, challenges, and perceptions among nursing faculty. These institutions, affiliated with esteemed health sciences universities, serve as hubs for nursing education, research, and practice, contributing significantly to the healthcare workforce and academic development within the region. The presence of a large number of nursing colleges underscores the breadth and depth of the nursing education system in Karnataka, providing ample opportunities for sampling and data collection to gain insights into the research culture and scholarly activities of nursing faculty members.

### Study population

#### Phase 1

The study population for Phase 1 will be comprised of nurse researchers affiliated with nursing institutions offering postgraduate programs in Karnataka, India. These nurse researchers include faculty members with postgraduate qualifications and above, as well as PhD scholars actively engaged in research endeavors within the specified region.

Specifically, participants for Phase 1 will be drawn from individuals who have participated in the survey conducted as part of the study. Furthermore, the inclusion criteria will require that participants have conducted at least one research study and have reported encountering at least one barrier as identified in Part 1 of the survey. This will ensure that participants have direct experience with the challenges and barriers associated with research publication.

Exclusions from the Phase 1 study population will encompass nurse researchers who have previously received training on the research publication process and those who are unwilling to participate in the study. This exclusion criterion will ensure a focused and representative sample for investigating the research publication experiences and challenges among nurse researchers within the targeted setting, without potential confounding factors introduced by prior training or lack of willingness to engage in the study.

#### Phase 2

Nurse researchers who demonstrate a willingness to publish, receive mentorship, and prepare manuscripts will be chosen as participants for Phase 2. The inclusion criteria will require that participants have given their consent to participate in the study and meet the eligibility criteria established during Phase 1.

Phase 2 will include mentors who are willing to engage in mentoring activities related to research publication and manuscript preparation. Preference will be given to mentors who possess an h-index greater than 5, indicating a significant level of research productivity and expertise in the field. These mentors will play a crucial role in providing guidance and support to nurse researchers throughout the publication process.

Pre-test assessments will be conducted for both the interventional and control groups, encompassing nurse researchers who meet the predefined inclusion criteria. These assessments cover key domains including knowledge, attitude, publication efficacy, and publication status, providing baseline data for evaluating the impact of the Mentored Writing Retreat Programme (MWRP) intervention.

**Sample size.**

**Phase 1:** The sample size for survey was calculated using the single population proportion formula,$$n=\frac{{\left(Z_{1-\frac{\alpha }{2}}\right)}^{2}pq}{{\left(d\right)}^{2}}$$

$Z_{1-\frac{\propto }{2}}$ = 1.96 at α = 0.05, *p* = Proportion, q = 1-p, d = allowable error (5% of p).$$n=\frac{{\left(1.96\right)}^{2}x\;\;0.61\left(1-0.61\right)}{{\left(.03\right)}^{2}}=317$$

Focus group discussions (FGDs) will be conducted until data saturation is achieved.

**Phase 2:** The sample size was derived using the formula for two independent groups,$$n=\frac{{\left(Z_{1-\frac{\alpha }{2}}+Z_{1-\beta }\right)}^{2}\sigma^{2}}{d^{2}},$$

$Z_{1-\frac{\propto }{2}}$ = 1.96 at α = 0.05, $Z_{1-\beta }$ = 0.84 at 80% power.

σ = Standard deviation difference of knowledge scores. d = Difference in pre- and post-intervention mean scores of knowledge.

The expected mean differences (d₁ = 2.26 and d₂ = 2.55) were derived from pilot observations conducted during preliminary implementation of similar training sessions.

To ensure a conservative and robust estimate, the average of the two values was considered for calculation:$$d=\frac{2.26+2.55}{2}=2.40$$

The pooled standard deviation was calculated using: $\sigma =\sqrt{\frac{\sigma_{1}^{2}+\sigma_{2}^{2}}{2}}$where:$$\sigma_{1}=20.7,\;\;\sigma_{2}=22.1\;\sigma =\sqrt{\frac{{\left(20.7\right)}^{2}+{\left(22.1\right)}^{2}}{2}}\approx 21.4$$

Substituting values into the formula:$$n=\frac{{\left(1.96+0.84\right)}^{2}\times {\left(21.4\right)}^{2}}{{\left(2.40\right)}^{2}}$$

The calculated sample size was 46 participants per group (*n* = 46), and an attrition rate of 10%, the required sample size per group is approximately 50 participants.

A total of 100 nurse researchers (50 in each group) who met the inclusion criteria were included in the second phase of the study.

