### Procedure for data collection

Phase I will begin with a quantitative survey to identify perceived barriers and facilitators among 317 nurse researchers across Karnataka. Following the survey, Focus Group Discussions (FGDs) will be conducted, each lasting 45–60 min with 10–12 participants, to gain deeper insights into thematic barriers and enablers.

The results from Phase I will guide the development of a Research Publication Manual and the MWRP intervention.

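### The Phase 1 survey size of 317 does not follow from its own formula, which gives 1,016; 317 respondents give a margin of about 5.4 points, not 3.

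*Protocol article*

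**What the plan says.** The sample size section of the protocol article states: "The sample size for survey was calculated using the single population proportion formula". The inputs are a two-sided 5% level with Z of 1.96, an expected proportion p of 0.61, and "d = allowable error (5% of p"). The section then substitutes 0.03 for d and gives the result as 317.

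The figure is carried forward. The abstract gives n = 317 for Phase I, and the data collection procedure plans a "quantitative survey to identify perceived barriers and facilitators among 317 nurse researchers across Karnataka".

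The only indication of population size is in the Setting section: "With over 500 nursing colleges distributed across Karnataka". That counts colleges, not nurse researchers, and the Phase 1 population is further limited to institutions with postgraduate programmes. No finite population correction, design effect or non-response inflation is given for Phase 1.

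**The concern.** The formula, every input and the result stand together in the text, and the two sides of the equation do not agree. The verbal and numerical definitions of d do agree with each other (5% of 0.61 is 0.0305, rounded to 0.03), so a slip in d alone is not an obvious explanation. The figure 317 also recurs elsewhere, so it is not a one-off misprint.

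This calculation is the only justification offered for the survey size. The survey is the quantitative part of the first objective and feeds the publication manual and the programme. A reader would infer from d that the survey proportions are known to within about 3 points. The article also presents itself as a method for others to replicate, and a team repeating this calculation would get a different number.

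**Working it through.** **Inputs** (all from the sample size section, Phase 1): Z = 1.96; p = 0.61; q = 0.39; d = 0.03 as substituted, or 5% of p = 0.0305 as defined; stated n = 317.

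**1. The plan's own expression.** n = Z² × p × q / d²

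- Numerator: 1.96² × 0.61 × 0.39 = 3.8416 × 0.2379 = 0.91392
- d = 0.03: 0.91392 / 0.0009 = 1,015.5, rounded up to **1,016**
- d = 0.0305: 0.91392 / 0.00093025 = 982.4, rounded up to **983**

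The stated 317 is not reproduced. 317 / 1,015.5 = 0.31, so the survey has 31% of the size its formula requires.

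**2. Other readings of the inputs.**

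| Change | n |
|---|---|
| d = 0.05 (absolute 5 points) | 365.6, so 366 |
| d = 0.06 | 253.9, so 254 |
| d = 0.061 (10% of p) | 245.6, so 246 |
| Z = 1.645, d = 0.03 | 715.3, so 716 |

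None gives 317.

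**3. Unstated adjustments that would reach 317.**

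- Finite population correction: setting n₀ / (1 + (n₀ − 1)/N) = 317 with n₀ = 1,015.5 gives N = 317 × 1,014.5 / 698.5 ≈ 460 (about 468 with d = 0.0305). The protocol gives neither a correction nor a count of eligible nurse researchers.
- d = 0.06 with 20% non-response: 253.9 / 0.8 = 317.3. This contradicts both the printed 0.03 and the 5%-of-p definition.

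**4. The precision that 317 delivers.** Half-width = Z × √(p × q / n)

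- At p = 0.61: 1.96 × √(0.2379 / 317) = 1.96 × 0.027395 = 0.0537, or **5.4 points**
- Relative to p: 0.0537 / 0.61 = 8.8%, against the stated 5%
- Against the stated 3 points: 5.37 / 3 = 1.8 times as wide
- At p = 0.5: 1.96 × √(0.25 / 317) = 5.5 points

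**5. Sensitivity to the unknown population size N.** Multiplying by √((N − 317)/(N − 1)):

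| N (assumed) | Half-width at n = 317, p = 0.61 |
|---|---|
| 500 | 3.25 points |
| 1,000 | 4.4 points |
| 2,000 | 4.9 points |
| 5,000 | 5.2 points |
| very large | 5.4 points |

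In the other direction, recruitment runs through institutional heads, email and professional networks. Similarity of respondents within institutions would multiply the half-width by the square root of the design effect. No design effect is given, so this cannot be quantified.

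**The case against.** The arithmetic itself cannot be defended. The objections concern its weight and the alternative figure.

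- **Weight.** Phase 1 is exploratory and descriptive. No hypothesis test depends on 317, Phase 2 has its own calculation, and the manual also draws on focus groups, literature and expert input. No named decision changes because a proportion is known to 5.4 points rather than 3. This stands as a limit on the consequence. It does not make the printed result right.
- **Implied harm.** The protocol does not say that survey results will be reported to within 3 points. The 3 points appear only as a sample size input, so reading them as the survey's precision is an inference, though a natural one. This also stands.
- **Certainty of 5.4 points.** The figure depends on simple random sampling, a large population and complete data. A small eligible population would narrow it, and clustering would widen it. This stands too, and the figure must carry its assumptions. It is nevertheless what the protocol's chosen formula gives at 317.
- **Which number is wrong.** The authors may have used an adjustment that the article omits. That is possible, but the article prints the complete calculation, and as printed it is false. An omitted adjustment would still require the passage to be corrected.

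**Conclusion.** The concern holds. The printed Phase 1 calculation yields 1,016 (983 with d unrounded), not 317, and no variant of the stated inputs that was tried gives 317. Under the formula's own assumptions (simple random sampling, a large population, p = 0.61, all 317 analysed), the 95% margin is ±5.4 percentage points, or 8.8% of p, against the stated 3 points and 5% of p. A documented small population would reduce that margin, and clustering by institution would increase it.

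The stated sample size and the stated precision cannot both be right, so the passage must be corrected. The effect is limited to how precisely the descriptive survey estimates its proportions.

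**What to change.** Replace the Phase 1 calculation with a statement of the precision achieved, for example: *With 317 respondents and an expected proportion of 0.61, the 95% margin of error is ±5.4 percentage points (8.8% of p), assuming simple random sampling from a large population and no allowance for clustering by institution.* Delete d = 0.03 and the 5%-of-p definition. Report the survey proportions with 95% confidence intervals, so that readers see the precision obtained.

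If 317 came from a finite population correction, a different d or a non-response allowance, state that adjustment with its inputs, including the population count and its source, and show the calculation that leads to 317.

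The cost is one corrected sentence and no additional respondents. The stated precision becomes less favourable.

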In Phase II, eligible participants (*n* = 100) will be randomly assigned to either an intervention (*n* = 50) or a control group (*n* = 50). The intervention group will participate in the MWRP, comprising three workshops conducted over a four-month period. The control group will receive no intervention during this period. Pre- and post-assessments will be conducted for both groups at baseline, as well as at four- and six-month post-intervention.

All data will be coded anonymously, stored securely, and accessible only to the principal investigator.

Recruitment and Allocation Procedures.

Participants for Phase I will be recruited from nursing institutions across Karnataka through official communication with institutional heads and dissemination of study information via email and professional networks. Eligible nurse researchers who meet the inclusion criteria and provide informed consent will be enrolled in the survey. Participants for focus group discussions will be purposively selected from survey respondents to ensure diversity of experiences and perspectives.

For Phase II, participants will be recruited from Phase I respondents who indicate willingness to participate in the Mentored Writing Retreat Programme (MWRP) and meet the predefined eligibility criteria. After obtaining informed consent, eligible participants will be enrolled and assigned unique identification codes.

Given the quasi-experimental design, participants will be allocated into intervention and control groups using a non-randomized approach. Allocation will be based on feasibility and participant availability, ensuring comparable group sizes (*n* = 50 per group). Efforts will be made to maintain baseline comparability between groups by considering key characteristics such as academic qualification, prior publication experience, and institutional affiliation.

The intervention group will receive the MWRP, while the control group will continue with routine academic activities without structured intervention during the study period. To ensure ethical fairness, the control group will be provided access to the training materials after completion of the study.

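### Phase 2 claims 80% power from a two-group formula, but its d is a pre-to-post change in trained people, and neither the group contrast nor the printed inputs support the claim

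*Protocol article*

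**What the plan says.** In the protocol article, the Phase 2 part of the Sample size section opens with "The sample size was derived using the formula for two independent groups". Its inputs are a Z of "1.96 at α = 0.05" and a Z of "0.84 at 80% power". The effect is defined as "d = Difference in pre- and post-intervention mean scores of knowledge" and the spread as "σ = Standard deviation difference of knowledge scores". On the source, it says: "The expected mean differences (d₁ = 2.26 and d₂ = 2.55) were derived from pilot observations conducted during preliminary implementation of similar training sessions". The two values are averaged to 2.40, and the section presents that average as the conservative choice. SDs of 20.7 and 22.1 are pooled to 21.4. The result is given as 46 per group, raised to about 50 for 10% attrition.

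The Phase II procedure, printed after the Research publication manual section, says of the comparator: "The control group will receive no intervention during this period". The Study design text has both groups take the same pre-test and post-test. The Data analysis section plans paired t-tests within groups and a repeated measures ANOVA between groups with control for baseline.

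**The concern.** In a two-group formula, d has to be the expected difference between the groups. Here it is a change over time in people who were trained. The two coincide only if the untreated group's mean does not move between tests. Controls answer the same 30-item questionnaire more than once over several months, so some retest or time gain is possible, and any gain shrinks the difference to be detected.

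This is the only power statement in the article. If it does not describe the intervention-versus-control comparison, a reader cannot tell what size of programme effect the trial is able to detect on knowledge.

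**Working it through.** **Inputs from the Sample size section.** Z values 1.96 and 0.84; d1 = 2.26, d2 = 2.55, d = 2.40 (the exact average is 2.405); σ = 21.4; n = 46 per group. The knowledge score runs from 0 to 30 (Study variables). The documents give no control-group change.

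**1. The plan's own figure.** The printed formula is (1.96 + 0.84)² σ² / d².

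- As printed: 7.84 × 457.96 / 5.76 = 623.3, not 46.
- With the factor 2 that a comparison of two means needs: 2 × 623.3 = 1,246.7.
- If 21.4 is read as a variance: 7.84 × 21.4 / 5.76 = 29.1, or 58.3 with the factor 2.

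None of these gives 46.

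**2. Which SD would make 46 right for d = 2.40?**

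- Printed form: √(46 × 5.76 / 7.84) = 5.81.
- With the factor 2: √(46 × 5.76 / 15.68) = 4.11.
- For comparison, 21.4 as a variance gives √21.4 = 4.63.

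None of these three SDs is stated in the article. They are assumptions used to show a range. The printed 21.4 is itself doubtful: a single score on a 0 to 30 scale cannot have an SD much above 15. A change score could in principle exceed that, because it can run from −30 to 30, but only if changes lay near the extremes.

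**3. Power for the between-group contrast.** Two-sided two-sample t-test (noncentral t), α = 0.05, 46 per group. The true difference is 2.40 minus the control gain; the gains are assumed.

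| SD assumed | Control gain 0 (difference 2.40) | Gain 0.5 (1.90) | Gain 1.0 (1.40) |
|---|---|---|---|
| 4.11 | 79% | 59% | 37% |
| 4.63 | 69% | 50% | 30% |
| 5.81 | 50% | 34% | 21% |
| 21.4 | 8% | 7% | 6% |

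**4. Is the average conservative?** The required n varies as 1/d², so the smaller d is the cautious one. Using 2.26 in place of 2.40 multiplies n by (2.40/2.26)² = 1.128, which takes 46 to 51.9. At SD 4.11 and 46 per group, power at 2.26 is 74% against 79% at 2.40.

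**5. Does the 80% hold for the before-after question instead?** At SD 21.4 and n = 46, a paired test of a 2.40 change has about 12% power. It does not.

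**The case against.** The strongest reply has three parts.

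First, the Data analysis section does plan paired t-tests and speaks of judging effectiveness by before-and-after means, so d fits an analysis in the plan. That is true. But a within-group change cannot separate the programme from retest or time effects, and the section itself claims a two-group sizing.

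Second, zero change in an untreated group is a common planning simplification. That stands too. At SD 4.11 with zero control gain, power is 79%, so the claim could be nearly right if both assumptions held. The fault is that neither is stated and the printed SD contradicts the second.

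Third, the larger defect is the arithmetic: at the printed SD, power is near the 5% floor whatever d means. This also stands, and it means that redefining d alone repairs nothing. The reverse holds as well: correcting the SD and the factor 2 would still leave d as the wrong contrast.

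The t-test powers above also take no credit for baseline adjustment, which could raise them. The article gives no correlation from which to judge by how much.

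A reader might also take d1 and d2 as the changes in two arms, which would make the between-group effect 2.55 − 2.26 = 0.29. The text does not support this: it says that both values "were derived from pilot observations conducted during preliminary implementation of similar training sessions", and neither is called a control value.

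**Conclusion.** The concern holds. As written, d is not an intervention-minus-control difference, the zero control change needed to make it one is unstated, and the average is wrongly described as conservative. The 80% power is unsupported for the between-group comparison and does not follow from the printed inputs either.

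The size of the shortfall cannot be fixed from the article. It depends on an SD that the article does not credibly give and on a control change that it does not give at all. Across the SDs shown, power at 46 per group runs from about 79% down to 8% with no control gain, and from about 59% to 7% with an assumed gain of 0.5 points.

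Two stronger conclusions should not be drawn. One is that the 80% is valid for the before-after question and merely misapplied; step 5 shows that it is not. The other is that a null between-group result could not be interpreted; an estimate with its confidence interval would still be informative, though the stated power could not be used to read it.

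**What to change.** In the Phase 2 part of the Sample size section:

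- Define d as the MWRP change minus the control change in knowledge, or as the baseline-adjusted post-test difference.
- Say what d1 and d2 are and which control change is assumed.
- Start from 2.26, or drop the description of the average as conservative.
- Give an SD that is valid for the chosen contrast on the 0 to 30 scale, with its source.
- Use the two-group formula with the factor 2.
- Keep 50 per group, and replace the 80% claim with the resulting power or the smallest detectable between-group difference. With n analysed per group, that difference is 2.80 × SD × √(2/n), or about 0.58 SD at n = 46.

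The items belong together: without a valid SD, neither replacement figure can be computed. The cost is a rewritten paragraph and probably a less favourable stated figure. No participants are added.
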